## Methods

### Trial design

The planned study (“IT-based relapse monitoring for schizophrenia”; acronym: ILIA) is a randomized-controlled (RCT), multicenter clinical trial evaluating the use of a smartphone- and web-based monitoring system for early warning signs of relapse integrated into standard clinical treatment, compared to treatment as usual (TAU) without digital monitoring. The study is conducted in outpatients with schizophrenia or schizoaffective disorders at 8 psychiatric hospitals in Munich, Augsburg and Berlin (Klinikum rechts der Isar, Ludwig-Maximilians-Universität (LMU) Klinikum, Isar-Amper-Klinikum München-Schwabing, München-Ost, Atriumhaus and Fürstenfeldbruck, Bezirkskrankenhaus Augsburg, Charité Universitätsmedizin Berlin). The inclusion is already possible at the end of an inpatient stay. The RCT is planned for 24 months, with the patients being recruited sequentially for 12 months. The intervention duration itself is 12 months. The protocol is registered in the German Clinical Trials Register (ID: DRKS00034991; registration date: 30.08.2024). An independent ethics committee reviewed and approved the research project (Technical University Munich, approval number: 2024-242-S-KK). The respective ethics committees of the participating clinics have followed the lead opinion of the ethics committee of the Technical University of Munich.

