### Sample size and recruitment

We aim for a sample size of *N* = 110 patients recruited from *n* = 8 clinics. The sample size calculation is based on the outcome “number of patients requiring inpatient psychiatric admission within one year.” A randomized pilot study using a simple text message-based solution to monitor early warning signs showed large effect sizes [28]. Since we expect the pilot study effect to be inflated and cluster effects present in our study, we opt for a considerable smaller, but still moderate effect (w = 0.30) for sample size calculation. Using a chi-squared test without cluster effects, a group size of 44 patients per group provides a power of 80% to detect a population effect of w = 0.30 with a two-sided Type I error rate of 5%. Assuming a dropout rate of approximately 20% [28], 110 patients need to be recruited. An approximately equal distribution across the eight centers is planned.

Identification of suitable patients and recruitment is supported by local clinicians in the clinics. Flyers and posters at local study sites support the recruiting process. Additionally, patients are recruited at external centers, such as counseling centers, assisted living groups, or self-help groups. To ensure a comprehensive recruitment process, social media is also included. Experienced study staff at the lead center, Klinikum rechts der Isar in Munich, and the Berlin study center are responsible for enrolling participants in the study, including obtaining informed consent. External patients are getting affiliated with one of the participating clinics for the duration of the study. They can choose to fully transfer to our outpatient clinics during the study period or remain with their local doctor while simultaneously attending the participating outpatient clinic.

A study phone will be provided for patients who do not own a private smartphone but still possess basic digital skills, such as using a PC or tablet, and having an internet connection at home. However, these cases are reviewed individually and thoroughly to ensure that no bias arises.

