### Outcomes

#### Baseline parameters

At baseline (T0), sociodemographic data (age, sex, nationality and language, educational background, family and occupation status) and history of illness (ICD-10 diagnoses, duration of illness, number of previous hospitalizations, previously prescribed medications, substance abuse) is collected via patient and clinician-rated questionnaires (Table 1).

**Table 1 Tab1:** Planned timepoints and data collection

Scale/item	Visit 0 (T0)	Visit 1 (T3)	Visit 2 (T6)	Visit 3 (T9)	Visit 4 (T12)
	Baseline	Week 13 +/- 3 weeks	Week 26 +/- 3 weeks	Week 39 +/- 3 weeks	Week 52 +/- 3 weeks
Written informed consent^a^	X^b^				
Screening/Assessment of inclusion/exclusion criteria^c^	✓^d^				
Sociodemographic characteristics	X				
Psychiatric diagnose(s) after ICD plus code	✓				
Change of psychiatric diagnosis(es)		✓	✓	✓	✓
Duration since first diagnosis	✓				
Number of previous episodes until now	✓				
Psychiatric comorbidities	✓				
Number of hospitalizations until now	✓				
Hospitalization days due to psychiatric illness in the past two years	✓				
Substance abuse	X	X	X	X	X
Alcohol abuse	X				
Smoking	X				
Currently psychiatric medication(s)	✓	✓	✓	✓	✓
Change and date in psychiatric medication(s)		✓	✓	✓	✓
Current other measures: e.g., psychotherapy, group therapy	✓	✓	✓	✓	✓
Rehospitalization (yes/no) and brief summary of admission reasons		✓	✓	✓	✓
Days in hospital since last study visit		✓	✓	✓	✓
Time to hospitalization		✓	✓	✓	✓
eHeals-g	X				
Questionnaire on prospective acceptance of eHealth	X and ✓				
Alarms since last study visit		✓	✓	✓	✓
Measures taken, if any, following the alarm		✓	✓	✓	✓
EWSQ-10P (control group only)	X	X	X	X	X
SDMQ-9	X	X	X	X	X
PAM13	X	X	X	X	X
ZUF-8	X	X	X	X	X
15-STARS	X	X	X	X	X
Question on Adherence	X	X	X	X	X
CGI-S/C	✓	✓	✓	✓	✓
PANSS-6	✓	✓	✓	✓	✓
FORSE	X	X	X	X	X
EuroHisQoL	X	X	X	X	X
WHODAS 2.0	X		X		X
SOFAS	✓	✓	✓	✓	✓
ANTISIDES	X				X
UKU-SERS self-rating	X				X
Mannheimer Resource Consumption Module	X				X
Reason for Dropout^e, f^ (if applicable)		✓	✓	✓	✓

^a^Written informed consent must be obtained at Baseline Visit 0 before data collection starts

^b^A X indicates the scale is patient-rated

^c^Screening can be done at Visit − 1 before Baseline or on the same day of Baseline at Visit 0

^d^A ✓ indicates the scale is clinician-rated

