### Data analysis

#### Analysis of quantitative data

The primary outcome parameter (psychiatric hospital admission) will be analyzed using a mixed model (logistic regression) with random intercepts for wards. Exploratory analyses of secondary outcome parameters will also be conducted: Differences in the time to hospitalization and simple relapses will be analyzed using a Kaplan-Meier curve and the log-rank test or within a generalized linear model framework (“Piecewise Exponential Model”). Additionally, we want to explore whether the effect of treatment is related with eHealth literacy and the acceptance of digital interventions with a subgroup analysis. Other secondary outcome parameters will be analyzed using mixed-effect regressions with random intercept for wards (logistic regressions if binary and linear regressions if continuous). If there are repeated measures available, this will be investigated within a multilevel framework, with random intercepts for subject and random slopes for time, if applicable.

Following the ITT principle, people that withdraw from the study (missing follow-up) need to be accounted for in the analysis. To deal with missingness, the primary analysis will adjust for baseline PANSS-6 score and age, since we expect these variables to be related to missingness. We expect an adjusted analysis to be the most efficient way to account for missing data in our experiment, mostly because of the binary outcome and the structure of missingness that is common in RCTs [51, 52]. The considerations for missing data will be subject to a sensitivity analysis. For this, missing values will be imputed with MICE (Multiple Imputation for Chained Equations) under a Missing at Random assumption. Imputation is an attractive alternative to our primary analysis, since there are many possible auxiliary variables measured at baseline that are not incorporated into the adjusted primary analysis. Additionally, in the case that there is a lot of dropout of similar structure (Reasons for Dropout), a sensitivity analysis under a MNAR assumption (pattern-mixture models) will be conducted.

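### Adding prior psychiatric hospital days to the primary model's covariates (PANSS-6 and age) would bring a modest gain in power; leaving them out is not an error

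*Protocol article*

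**What the plan says.** The protocol article (Analysis of quantitative data) specifies a logistic mixed model for psychiatric admission with a random intercept per ward. It names two covariates and gives one reason for them: "the primary analysis will adjust for baseline PANSS-6 score and age, since we expect these variables to be related to missingness". Whether they predict admission is not discussed. The same section acknowledges that many other baseline variables stay out of this model and could serve as auxiliaries in a multiple-imputation sensitivity analysis.

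Table 1 (Baseline parameters) includes "Hospitalization days due to psychiatric illness in the past two years", rated by the clinician at T0, and also the lifetime number of hospitalizations. Neither is named as a covariate.

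The sample is mixed with respect to hospital history. Under Trial design, "The inclusion is already possible at the end of an inpatient stay". Under Participants, others qualify through a relapse up to two years back, which may be a symptom increase without admission, and patients whose illness began less than three years ago are exempt from the relapse criterion.

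The sizing takes no credit for covariates. "Using a chi-squared test without cluster effects", it finds that "a group size of 44 patients per group provides a power of 80% to detect a population effect of w = 0.30", and after allowing for dropout that "110 patients need to be recruited".

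**The concern.** Covariates in a randomized trial are usually chosen because they predict the outcome. Here the only stated criterion is a relation to missingness, which is incomplete even for its own purpose: in an analysis of observed outcomes, adjustment removes bias from dropout only where the covariate relates to the outcome as well. A baseline measure of past psychiatric hospital use is the same kind of quantity as the primary outcome. The footnotes to Table 1 list clinical deterioration among the dropout reasons, so hospital history could bear on both.

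Two things are at stake. One is some power in a trial sized at the 80% margin. The other is exposure of the primary result to a chance difference between arms in recent hospital use, which PANSS-6 and age may not absorb.

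**Working it through.** **Inputs from the protocol article.** Two-sided alpha 5%, w = 0.30, 44 per group, about 20% dropout, 110 recruited (Sample size and recruitment); 1:1 allocation (Randomization and blinding); 12-month readmission of about 40% in schizophrenia and 28% in schizoaffective disorder (Introduction). The last two rates are background figures, not stated sizing inputs; they are used here as control-rate scenarios.

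**1. The plan's own figure.** N = (1.960 + 0.842)² / 0.30² = 87.2, so 88, or 44 per group. With 1 degree of freedom and noncentrality N·w², power is 80.35% at N = 88 (79.9% at 87). Dropout: 88 / 0.8 = 110. The stated figures reproduce.

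**2. Events implied.** For two equal groups, w = (p₁ − p₂) / (2√(p̄(1 − p̄))).
- Control 40%: w = 0.30 gives p₂ = 13.4%; events 44 × (0.400 + 0.1345) = 23.5.
- Control 28%: w = 0.30 gives p₂ = 5.6%; events 44 × (0.280 + 0.0557) = 14.8.

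So roughly 15 to 24 events are expected among 88 evaluable patients.

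**3. Effect of adding the covariate.** Simulation: 88 evaluable patients, 3,000 trials per setting. The logistic model contains treatment and two covariates standing for PANSS-6 and age (assumed OR 1.2 per SD each), with or without a third standardized covariate for prior hospital use. Treatment is tested by likelihood ratio; ward intercepts are omitted. The strength of the third covariate is assumed.

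| OR per SD | Power, control 40% | Relative efficiency of risk difference | Power, control 28% |
|---|---|---|---|
| 1.0 | 82.4 → 82.4% | 0.99 | 83.2 → 83.1% |
| 1.25 | 83.7 → 83.6% | 0.99 | 84.1 → 83.6% |
| 1.5 | 83.4 → 84.7% | 1.02 | 84.1 → 85.0% |
| 2.0 | 83.6 → 86.2% | 1.07 | 83.6 → 85.3% |
| 2.5 | 84.3 → 87.9% | 1.12 | 84.0 → 87.7% |

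Only the differences should be read; the absolute level depends on the test. A separate simulation gave +3.5 points at OR 2.0 and +4.5 at 2.5 for the 40% scenario, hence +2 to +4 and about +4 as summary values. At 28%, between 2,749 and 2,785 of the 3,000 trials could be fitted, so about 7 to 8% were lost to sparse events and that column is less secure.

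**4. Where the gain lies.** The standard error of the treatment log odds ratio rose in every setting, for example 0.565 → 0.607 at OR 2.0 and a 40% control rate. In logistic regression a prognostic covariate also moves the conditional estimate away from the null. Where the covariate is strong enough, that movement outweighs the larger standard error and power rises.

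**5. Type I error.** At a 40% risk in both arms it was 5.6% without the covariate, and with it 5.6% (OR 1.0) and 6.3% (OR 2.0). The simulation error of each rate is √(0.06 × 0.94 / 3000) = 0.43 points. Other runs put the increase at half a point or less (6.1% against 6.6% in one).

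**6. Chance imbalance.** With 44 per arm, the SD of the between-arm difference in a standardized covariate is √(2/44) = 0.213, so a difference of at least 0.3 SD (0.3 / 0.213 = 1.41) arises in about 16% of trials. In those trials, under no treatment effect and 40% risk, omitting the covariate gives:
- OR 2.0: median shift of 0.23 in the treatment log odds ratio; conditional type I error 9.1%, against 6.9% with the covariate.
- OR 2.5: median shift of 0.30; conditional type I error 9.4%, against 5.6%.

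With the covariate included, the shift is near zero.

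**The case against.** The strongest reply is that this is a defensible, openly stated choice. The protocol says that other baseline variables are left out and offers an imputation sensitivity analysis that can use them. An analysis plan not shown could still extend the covariate list. Nothing in the documents says how strongly past hospital use predicts readmission, and eligibility partly selects on recent relapse, which may narrow its spread. Events are few and already shared by treatment, two covariates and ward intercepts.

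Most of this stands, and it limits the point to an improvement. It does not dispose of it: the imputation analysis is a sensitivity analysis and does not put hospital history into the primary model, and the protocol does fix the primary covariates and the reason for them.

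A reader might infer more than the documents support:
- **That precision of the planned odds ratio is being lost.** Its standard error does not fall when the covariate is added.
- **That the gain is free.** If the covariate is weak, relative efficiency is 0.98 to 0.99.
- **That prior hospitalization is known to be the strongest predictor.** The protocol gives no figure for it.
- **That the sample size is wrong or the comparison biased.** N = 110 reproduces without any covariate. Randomization leaves the comparison unbiased on average, and the overall error rate already includes chance imbalance; adjustment helps in the particular trials where imbalance occurs.

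**Conclusion.** The point holds as a modest, inexpensive improvement to the primary model, not as an error. At the plan's own effect size and a 40% control rate, adding prior hospital days changes power by about 0 points at an OR per SD of 1.25 or less, about +1 at 1.5, +2 to +4 at 2.0 and about +4 at 2.5. It also lowers the false-positive risk in the roughly one trial in six with a noticeable imbalance in recent hospital use, if the covariate is prognostic. The downside is a 1 to 2% efficiency loss if it is weak, and type I error higher by at most about half a point within simulation error.

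The size rests on the assumed covariate strength, on control rates taken from the Introduction, on a normally distributed covariate independent of PANSS-6 and age, and on leaving out ward effects.

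**What to change.** In Analysis of quantitative data, add log(1 + psychiatric hospital days in the past two years) as one further pre-specified covariate in the primary model, with a prognostic reason, before outcome data are seen. Keep baseline PANSS-6 and age. The logarithm limits the influence of a few very long stays.

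Do not also add an indicator for recruitment at the end of an inpatient stay: Table 1 lists no such item, and a further term would draw on scarce events. Because Randomization and blinding places allocation ahead of the baseline assessment, take the hospital-day count from records where possible, so that knowledge of the arm cannot influence it.

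The cost is one line of text and one model parameter; the variable is already collected. The sample size need not change.

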#### Analysis of qualitative data

For the qualitative approach, semi-structured interviews will be used to undergo a process evaluation analysis, to evaluate and explain the outcomes [53, 54]. The interview protocol will be adapted by previous protocols of clinical intervention studies conducted by the research group in this target population [47–49]. We will take recordings of patient-clinician dyads for the purpose of conducting conversation analyses based on conventions developed by Gail Jefferson [55], to observe direct interactions during treatment and utilization of the digital intervention. Basic and fine-grained transcripts will be prepared for selected relevant sections to examine the conversations with regard to the themes of shared decision making, fear of relapse and treatment adherence. The dyadic records are also analysed in a structured content analysis [56]. This approach allows for fully inductive categorization of the material, deductive categorization, and a combination of both through a multi-stage process and coding.

## Discussion

Digital interventions have emerged as promising tools for supporting patients with schizophrenia or related psychotic spectrum disorders, especially in the critical post-hospital discharge phase [57–59]. These interventions encompass a wide range of applications, from symptom monitoring and relapse prevention to cognitive training and psychosocial support [60–62]. Digital tools can provide ecologically valid data for clinicians, contributing to more accurate, informed decisions and better personalized and proactive care [63]. These low-threshold interventions can empower patients to take an active role in their treatment and be more involved, thereby enable more autonomous health actions [64].

Interview data reveals that patients with schizophrenia often overestimate their health status and underestimate their risk of relapse [65]. This tendency stems from a limited ability to recognize early warning signs, leading to maladaptive behaviors during critical phases. Given the high relapse rate in schizophrenia or schizoaffective disorder and associated costs, those results underscore the need for improved risk awareness and timely, accurate communication between patients with schizophrenia and clinicians, to manage relapse risk effectively [65]. By providing comprehensive symptom monitoring and fostering patient autonomy, digital interventions can contribute to more effective and timely relapse prevention strategies. A pilot RCT showed that text message-based relapse prevention measures are highly acceptable and easy to understand for patients with schizophrenia or a schizoaffective disorder and can improve patient-clinician communication [66].

While research on blended care with digital solutions for patients with schizophrenia is expanding, the findings remain tentative at best, and the widespread integration of tailored digital tools at a national level is still largely absent [67]. Previous text message-based early warning sign monitoring solutions followed a paternalistic medical approach and focused solely on the actions of the clinicians, excluding patients from the information loop and no visual feedback on the disease development was provided to neither the patients, nor clinicians [28, 66, 68]. Accordingly, the effects on reduced hospitalizations depended mainly on the behavior of the clinicians, whether and how quickly they reacted to the text message-based relapse alert [28, 69, 70]. To our knowledge, only one cluster-randomized trial exists that used a smartphone-based intervention to prevent relapse in people with schizophrenia by monitoring early warning signs [71, 72]. Their smartphone app required daily monitoring with up to 56 items per assessment, delivered empowerment impulses to participants and assistance provided by peer-support workers. However, to our knowledge, no validated questionnaire was included, the intervention did not provide a digital interface and feedback loop to the treating clinician, and no joint action between the patient and the treating clinician was mandatory. Additionally, the number of assessments during the 12-month intervention period appears to be quite burdensome. The study did not focus on the assessment of hospitalization measures (e.g. days spent in hospital, time to hospitalization) as main indicators of effectiveness on relapse.

With our study we expect that the continuous digital monitoring of early warning signs by patients and the participatory treatment decision-making process together with their clinicians, will lead to behavioral changes, thereby reducing the necessity and duration of psychiatric hospital stays of patients, as well as healthcare costs. Furthermore, the intervention could improve symptomology, medication adherence, fear of relapse, satisfaction, social functioning, patient activation and shared-decision making. The insights gained from this study can be applied to routine psychiatric care, sustainably enhancing the treatment of patients with schizophrenia and schizoaffective disorder.

## Abbreviations

RCT: Randomized-controlled trial
TAU: Treatment as usual
EWSQ-10P: Early-Warning-Signs Questionnaire – 10 items, Patient Version
T0: Baseline Assessment; First Study Visit
MICE: Multiple Imputation with Chained Equations
